## Abstract

**Background:**

Higher than expected adolescent pregnancy high rates continue globally, with repeated unplanned pregnancy (UP) in this age group is a public health problem. In Brazil, 16% of pregnancies occur in adolescents under 18 years old, with high maternal morbidity and mortality rates in this age group. Effective and safe contraception is required to reduce UP rates. The objective of our study is to evaluate acceptance of etonogestrel (ENG)-releasing subdermal contraceptive implant after childbirth, before discharge, as well as clinical performance up to one year after placement. Comparison between teenagers who opt for ENG-implant versus other contraceptive methods after childbirth will be also evaluated, specifically regarding UP, continuation and discontinuation rates and reasons, body composition, pelvic ultrasound characteristics and user satisfaction.

**Methods:**

A non-randomized open-label trial will be conducted with teenagers after childbirth and followed up to one year at the Women’s Hospital, University of Campinas (UNICAMP), Campinas, Brazil. The study group will consist of patients who accepted to use ENG-implant and placed before discharge. The comparison group will include adolescents who choose to use other contraceptive methods at the first postpartum visit (42 ± 3 days after childbirth). All women will follow-up at 40–60 days postpartum, as well as, at 6 and 12 months post-enrollment. Patient satisfaction, contraceptive effectiveness, reasons of discontinuation, continuation rate and body composition will be evaluated. Transvaginal ultrasound and electric bio impedance tests will be performed at all follow-up appointments. A 5% significance level was assumed, as well as, a sampling error (absolute) for 10% prevalence. The sample size was calculated at *n* = 100, obtaining an estimate of 50 to 70 adolescents who would accept the method offered, according to the prevalence and sample error assumed.

**Discussion:**

Long-acting reversible contraceptive (LARC) methods include subdermal implants and intrauterine contraceptives, are considered first line contraception for teenagers. Immediate postpartum use is a safe option, which significantly reduces rates of repeated UP and all the undesirable consequences inherent to this process.

**Trial registration:**

This study was approved by the Ethics and Research Commission of UNICAMP (CAAE: 92869018.5.0000.5404) and the Brazilian Registry of Clinical Trials (REBEC): http://www.ensaiosclinicos.gov.br/rg/RBR-4z7bc6, (number 2.901.752).

## Plain ENGLISH summary

Long-acting reversible contraceptives (LARC), which include the subdermal implant, are considered first line for teenagers. Immediate postpartum use is a safe option, which significantly reduces rates of repeated unplanned pregnancies, as well as all the undesirable consequences inherent to this process.

The aim of this protocol is to evaluate acceptability of the use of subdermal implant during the immediate postpartum period, its contraceptive efficacy, adverse effects and reasons for discontinuation over a one-year period. In addition, information regarding the relationship between implant use and body composition, ovarian ultrasound characteristics and user satisfaction were analyzed and compared to a group of teenagers using other contraceptive methods started during the postpartum period.

All patients aged up to 19 years, who give birth at the Woman’s Hospital will be invited to participate in the study prior to hospital discharge, and when the patient chooses to use the subdermal implant, it will be inserted immediately. The women that opt for other contraceptive methods, they will be offered at the return between 40 and 60 days postpartum. All women will follow-up at this first visit postpartum as well as at 6 and 12 months post-enrollment.

Our expectation is that almost 60% of the adolescents after childbearing at our hospital will choose the subdermal implant as contraceptive method due to the higher contraceptive efficacy when compared to non-LARC methods and few side-effects mainly abnormal uterine bleeding, with a high rate of continuation and satisfaction.

## Background

Pregnancy at adolescent age is higher than expected worldwide, particularly in low and middle-income countries (LMIC) and in Latin American and the Caribbean (LAC) countries is very high. Rates in LAC countries are the second highest, surpassed only by sub-Saharan African countries, at 66.5 in 1000 women. In Brazil, 16% of pregnant women are in this age group, with highest parity seen in those who became pregnant before the age of 20, representing the part of the population that contributes to continued high total fertility rates [1, 2].

Maternal mortality is one of the main causes of death in teenagers and young women up to 24 years of age. This, alongside maternal morbidity and near misses, are far more frequent when pregnancy occurs before the age of 15, when preeclampsia, postpartum hemorrhage and anemia are the main causes [3, 4]. Additionally, pregnant adolescent also present an increased risk of prematurity, small for gestational age (SGA) newborns and increased perinatal and childhood morbidity and mortality [5].

Multiple strategies have been adopted aiming to reduce these numbers, with educational interventions and promotion of effective and safe contraceptive methods for teenagers among the measures with the greatest positive impact [6]. UP among teenagers is a consequence to improper and/or lack of use of contraceptive methods [7]. LARC methods, which include subdermal implants and intrauterine contraceptives (IUCs) are the first line for this age group [8–10].

LARCs are the most effective reversible contraceptives, with a pregnancy rate of less than 1/100 women/year, as well as a high satisfaction, low discontinuation and high continuation rate in teenagers [8, 9]. Subdermal implants are one of the best method, with a failure rate of 0.4/100 women/year [11, 12]. In addition, immediate postpartum use is highly recommended, because it is a time when women are prone to prevent a new pregnancy and due to the fact that many women are unable to return to a health facility or do not have access to a LARC method [11, 13–16].

Despite LARC being recommended as the method of choice in these women, less than 5% of health professionals prescribe and insert them [8, 17]. Care and guidance on postpartum contraception during antenatal care is essential in planning and choosing the best method to prevention of new pregnancies in the short term [18].

Otherwise, placement of the ENG-implant is considered safe during breastfeeding and do not presents maternal, neonatal or postpartum risks [11, 13–16]. with no risk of expulsion as occurred with IUC [19].

Also, teenagers presented a high adherence rate when using LARC, with rates of 84 and 74% for the subdermal implant and IUD, respectively [20]. Abnormal uterine bleeding is cited as the main reason for withdrawal of the method [21].

However, a study with women who opted for insertion of the ENG- implant during the immediate postpartum period and followed-up over 3 years, showed that teenagers, who represented 28.2% of the sample, had high continuation rate (94.5%) [22].

The repetition of an UP among teenagers is associated with a low level of schooling, drug addiction and incorrect use of contraceptives among other causes [23]. In this population, the incidence of a new pregnancy within 2 years after the first one was 35%; however, with placement of any LARC at the immediate postpartum period, the rate decreased by 88.2% when compared to non-LARC methods [24].

The aim of our study is to evaluate acceptability, contraceptive efficacy, discontinuation rate by reasons and continuation rates among adolescents who either accept the ENG-implant versus non-acceptors at the immediate postpartum period and follow-up up to one year after placement. In addition, information regarding the relationship between implant use and body composition, pelvic ultrasound characteristics and user satisfaction will be analyzed in both groups.

## Methods/design

### Study type

A non-randomized and open-label trial.

### Setting

The study will be conducted at the Department of Obstetrics and Gynecology, University of Campinas Medical School, Campinas, Brazil. The facility is a tertiary referral public hospital wich offer treatment and it is referral for approximately 60 municipalities, covering a population of more than five million inhabitants.

### Inclusion and exclusion criteria

The inclusion criteria are all women aged up to 19 years old, who give birth at our hospital, and are invited to participate in the study prior to hospital discharge. Exclusion criteria are those who chose to not use any contraceptive method, or present an absolute contraindication to the use of the contraceptive methods offered according to the World Health Organization (WHO) eligibility criteria [25], as well as, those who are unable to attend follow-up appointments during the proposed study period.

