### Sample size

The sample size was calculated based on a prevalence of acceptance of the ENG-implant, based on the satisfaction of teenagers users with the implant [27]. A significance level of 5% and a sampling error (absolute) for the prevalence of 10% were assumed (expected prevalence between 50 and 70%). The formula is based on a binomial distribution (satisfied or not satisfied) n = Z21-a/2 p(1-p) / e2, since e = sampling error of prevalence, p = estimated prevalence (based on literature), a = significance level and Z is the value of normal distribution. The sample size was calculated in *n* = 92,2 and rounded to 100 to contemplate casual lost in the sample. We expected obtaining an estimate of between 50 and 70 teenagers who will accept the method, according to the prevalence and sample error assumed. After collecting the data, the groups will be compared for the dependent variables and the power of the test will be calculated for user satisfaction, method effectiveness, side-effects, body composition, and ultrasound evaluation. The expected flowchart from the study is in Fig. 1.

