## Discussion

Our expectation is that almost 60% of the adolescents after childbearing at our hospital will choose the ENG-implant as contraceptive method due to the higher contraceptive efficacy when compared to non-LARC methods and few side-effects mainly abnormal uterine bleeding. Breakthrown or unscheduled bleeding after ENG-implant placement is the main reason for early discontinuation; however, we expected that in this particular group of users, due to the physiological bleeding after childbearing, this side-effect could be avoided, they will be satisfy and continuation rate could be high than when placement of ENG-implant occurs at interval period.

In addition, it is unlikely that body composition will be affected with the use of the ENG-implant, because it was described that the weigh gain is almost one kg/year after implant placement, with most patients likely to present normal pelvic characteristics during ultrasound scans.

The large number of UP among Brazilian adolescents and young women is one of the main sexual and reproductive health public problem. One of the consequences is the high cost for the national health service of approximately US$ one billion per year and childbearing at adolescent age contribute significantly to this burden [29]. According to data from the Brazilian Ministry of Health, approximately 20% of all pregnant women are teenagers and, ~ 60% are UP. Therefore, we consider that our study could be a demonstration one to provide reliable data on one strategy about how to reduce these indices.

LARC methods, including the ENG-implant are the first option to reduce UP in teenagers [30]. However, there are few studies in the literature that assess its use in this specific population.

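### Implant acceptance is estimated after removing women who choose no contraceptive method, all of them non-acceptors, yet the expected 60% is attributed to adolescents delivering at the hospital

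*Protocol article*

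**What the plan says.** The Abstract puts acceptance first: "The objective of our study is to evaluate acceptance of etonogestrel (ENG)-releasing subdermal contraceptive implant after childbirth, before discharge". The last paragraph of the Background section also lists acceptability as the first aim.

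The Sample size section ties the number of participants to the same quantity: "The sample size was calculated based on a prevalence of acceptance of the ENG-implant, based on the satisfaction of teenagers users with the implant". It continues: "A significance level of 5% and a sampling error (absolute) for the prevalence of 10% were assumed", with "expected prevalence between 50 and 70" percent. The result is: "The sample size was calculated in *n* = 92,2 and rounded to 100 to contemplate casual lost in the sample". From these 100 the authors expect 50 to 70 acceptors.

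The Inclusion and exclusion criteria invite all women up to 19 years who deliver at the hospital, then remove three kinds of women: "Exclusion criteria are those who chose to not use any contraceptive method", those with an absolute contraindication, and "those who are unable to attend follow-up appointments during the proposed study period". The Intervention section divides participants into two groups only, implant acceptors and women taking another method at the 40–60 day visit. There is no group for women using no method.

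The Discussion, and the plain-language summary in nearly the same words, expects that "almost 60% of the adolescents after childbearing at our hospital will choose the ENG-implant".

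**The concern.** Acceptance of an offer is the number of women who take it divided by the number who were offered it. A woman who is counselled, offered the implant and leaves without any method has declined the offer. The eligibility criteria take her out of the sample from which acceptance is read. This is selection on the outcome itself and it works in one direction, because choosing the implant and choosing no method are mutually exclusive.

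The reported percentage would then describe implant choice among adolescents who took some method and could be followed. The Discussion presents the study as a demonstration of a strategy to reduce unplanned pregnancy. For that purpose the reader needs uptake among those offered, and the text attributes the figure to that wider population. The confidence interval does not cover this kind of error, and enrolling more women does not shrink it.

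**Working it through.** **1. The plan's own figure.** Inputs from the Sample size section: two-sided 5% level (z = 1.96) and absolute error e = 0.10. The value p = 0.60 is the midpoint of the stated range and matches the expectation in the Discussion.

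n = z² p(1 − p) / e² = 3.8416 × 0.24 / 0.01 = 92.2, as stated. Other values do not match: p = 0.50 gives 96.04 and p = 0.70 gives 80.67. With n = 100 and p = 0.60 the 95% half-width is 1.96 × √(0.24/100) = 0.096, or 9.6 points.

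**2. The implied denominator.** Expecting 50 to 70 acceptors from n = 100 restates the 50–70% prevalence with the enrolled sample as denominator, that is, after the exclusions. No other denominator for acceptance is stated.

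**3. Effect of the no-method exclusion.** Take 100 eligible women offered the implant, of whom 60 accept and 40 decline. Let f be the share of decliners who choose no method and are excluded. The document does not give f, so it is assumed here.

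Observed acceptance = 60 / (100 − 40f)

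| f (assumed) | Excluded per 100 offered | Observed acceptance | Bias (points) |
|---|---|---|---|
| 0.10 | 4 | 60/96 = 62.5% | +2.5 |
| 0.20 | 8 | 60/92 = 65.2% | +5.2 |
| 0.30 | 12 | 60/88 = 68.2% | +8.2 |
| 0.40 | 16 | 60/84 = 71.4% | +11.4 |

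The bias equals 10 points when 60 / (100 − 40f) = 0.70. Then 100 − 40f = 85.7 and f = 0.357, about 14 women per 100 offered.

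**4. The same effect read backwards.** Suppose the trial observes 60% and a share x of all counselled women was excluded for choosing no method (x assumed). True acceptance is 0.60 × (1 − x): 57% for x = 5%, 54% for x = 10%, 48% for x = 20%. The gap reaches 10 points at x = 0.10/0.60 = 16.7%. This threshold differs from the 14 per 100 in step 3 because here the observed figure is fixed at 60%, and there the true one is.

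**5. Women unable to attend follow-up.** Let y be their share and q their acceptance, both assumed, with 60% observed in the rest. True acceptance = 0.60 × (1 − y) + q × y. For y = 20%:

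- q = 30% gives 54%, so the reported figure is 6 points too high.
- q = 60% gives 60%, no bias.
- q = 80% gives 64%, so the reported figure is 4 points too low.

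The sign depends on q, which is not given. With both exclusions, x = 10%, y = 10% and q = 30% give 0.60 × 0.80 + 0.03 = 51% (9 points too high). With x = 5%, y = 20% and q = 80% the result is 0.60 × 0.75 + 0.16 = 61% (1 point too low).

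**6. Sample size.** A lower true acceptance hardly changes n: 95.4 at p = 0.54, 95.9 at p = 0.48, and a maximum of 96.04 at p = 0.50. All are below 100.

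**The case against.** Several points on the other side carry weight.

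- **The exclusion is openly stated and the narrower quantity is legitimate.** Acceptance among adolescents who choose some method is a valid descriptive figure. This stands, but it is not the population to which the summary and Discussion attach the 60%.
- **The denominator is inferred.** No sentence defines it, and the flowchart is not available here, so it may contain a box for women invited or refusing. A condensed article may also leave a screening log to the full protocol. The absence of a log is therefore not the finding. The finding is that the stated exclusion, the two-group structure, the 50–70 out of 100 and the population claimed do not fit together.
- **Sizing on acceptance is not wholly clean.** The Sample size section takes its prevalence from satisfaction data and describes the binomial outcome as satisfaction. Its opening sentence and its expected yield are nevertheless about acceptance.

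A reader might also infer three stronger things, which the documents do not support:

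- **That excluding women who cannot return inflates acceptance too.** The Background section uses inability to return as an argument for immediate postpartum placement, so these women might accept more often. The direction is open.
- **That decliners who take no method at 40–60 days certainly leave the denominator.** The Intervention section defines the comparison group by method taken at that visit, which suggests so. The Follow-up section schedules all participants and counts non-attenders who cannot be reached as lost to follow-up, which would keep them among those enrolled. The text is ambiguous.
- **That the bias exceeds the planned error.** This needs about 36% of decliners to be removed, and nothing in the document supports or rules out that share. At 10% to 30% the bias is 2.5 to 8.2 points, inside the planned 10.

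**Conclusion.** The point holds for the no-method exclusion. Given that acceptance is calculated on the enrolled sample, as the expected yield implies, the effect of this exclusion is upward with certainty. Its size cannot be derived from the document: 2.5 to 11.4 points for an assumed 10% to 40% of decliners removed, starting from a true acceptance of 60%. The exclusion of women unable to attend makes the estimate less representative of adolescents delivering at the hospital, without a known sign, so the net effect of both exclusions is not certain to be upward. The fault lies in the denominator and the population claimed. The sample size is adequate either way.

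**What to change.** 1. Define acceptance as implant acceptors divided by all adolescents counselled and offered the implant before discharge who have no contraindication to it. Count those who choose no method as non-acceptors, and keep decliners in the denominator whatever happens at 40–60 days.
2. Apply the no-method exclusion only to the follow-up comparison between implant users and users of other methods.
3. Report how many women were excluded as unable to attend follow-up. Where their choice was recorded, show acceptance with and without them. No choice need be sought from women to whom the implant was not offered.
4. If this is not done, restrict the 60% statements in the plain-language summary and the Discussion to adolescents who choose some method and can be followed.

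The cost is a simple log of offers and choices, started with recruitment because women not recorded then cannot be recovered later. The headline acceptance figure will probably be lower. The required n stays at or below 96.04, within the planned 100.

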### Intervention

Placement of ENG-implant (Implanon NXT, MSD, Oss, The Netherlands) at the immediate postpartum period (up to 48 h after childbearing). This method is not yet offered as routine in the hospital. After properly counselling (including effectiveness, characteristics, possible adverse effects, shelf-life use, and options to change the contraceptive method chosen after enrollment), the participants will be divided in two groups: 1) study group among those who chose ENG-implant and will receive it prior to hospital discharge and 2) non-acceptors of implant and acceptors of other contraceptive methods at the first follow-up between 40 and 60 days postpartum.

### Follow-up

All participant women will be schedule to return to postpartum visit up at 40–60 days, and again at 6 and 12 months post-enrollment. Patient satisfaction, contraceptive effectiveness, rates and reasons of discontinuation and continuation rate, as well as, body composition will be evaluated. Transvaginal ultrasound and electric bio impedance tests will be performed at all follow-up appointments. Non-implant acceptors will start follow-up at the 40–60 day after childbearing. Efficacy, characteristics, and contraindications will be based on the WHO criteria [25]. Women who do not attend the schedule follow-up visits and those who we were unable to contact after three telephone call will be consider lost-to-follow-up (LFU).

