### Statistical analysis

The data will be recorded in a data collection sheet prepared for this study. The encrypted data will be stored anonymously in a excel database, after manual review and double typing for descriptive statistical analysis (mean, standard deviation, absolute and relative frequency distribution). The association between independent and dependent variables will be performed using the X^2^test (for qualitative variables) or Fisher’s exact test (when 25% or more of the expected values ​​are less than 5) and through the Student’s *t* test (or the Mann-Whitney test if the data do not present normal distribution, as well as logarithmic, inverse and quadratic transformations of the same). Open questions will be categorized for application of statistical analyzes as well as qualitative variables. Additionally, we will estimated the couple year protection (CYP) which is an indicator of the number of pregnancies averted in each of the groups under evaluation. The level of significance adopted for the statistical tests will be 5%. For statistical analysis, the program Statistical Analysis System (SAS), version 9.4 will be used. Other procedures will be adopted for quality control. Each patient will have an identification number so as not to permit confusion of data, the completed forms will be reviewed and the data put on to the database by two different typists in order to avoid losses and typing errors. All material used for data collection will be stored by the researcher for five years, remaining confidential. This article has followed the SPIRIT guidelines for its elaboration [28].

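### One-year continuation, discontinuation by reason and pregnancy are to be compared with fixed-denominator tests that cannot use the partial follow-up of women lost before 12 months

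*Protocol article*

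**What the plan says.** **Outcomes.** The aims at the end of the protocol article's Background include "discontinuation rate by reasons and continuation rates among adolescents", for implant acceptors against non-acceptors, followed for up to one year. The Abstract adds unplanned pregnancy to the comparison.

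**Follow-up.** Visits fall at 40–60 days postpartum and at 6 and 12 months after enrolment. Implants are placed within 48 hours of birth, whereas follow-up of the comparison group starts at 40–60 days. The women considered lost to follow-up are "Women who do not attend the schedule follow-up visits and those who we were unable to contact after three telephone call".

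**Methods.** The Statistical analysis section begins with descriptive statistics, including relative frequencies. It continues: "The association between independent and dependent variables will be performed using the" chi-square test for qualitative variables, or Fisher's exact test when expected counts are small. The t or Mann-Whitney test serves the remaining variables, and couple-year protection is an added indicator. "The level of significance adopted for the statistical tests will be 5"%. No method for censored data is named.

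**Losses.** The Sample size section foresees them. The calculated number is "92,2 and rounded to 100 to contemplate casual lost in the sample". No loss rate is given.

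**The concern.** Stopping a method and becoming pregnant are events in time, and women will be observed for different lengths of time. Reasons for stopping compete, since a woman who stops because of bleeding can no longer stop for another reason. A chi-square or Fisher test needs one final status per woman. A woman who attends at 6 months, still using her method, and is then lost has to be left out or given a status nobody observed. Her six months of known continuation cannot be used.

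The loss rule adds an ambiguity. Its conjunction may describe one group (visit missed and calls failed) or two groups, either of which counts as lost. On the second reading, a woman who misses a visit is lost even if a call establishes whether she still uses the method.

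At stake are the continuation and reason-specific rates, which are named aims, and the test between groups. Loss could plausibly differ between groups. They are self-selected, and one is followed from birth while the other is followed from 40–60 days.

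**Working it through.** **1. The plan's own figure.** Formula: n = z² p(1 − p)/e². The inputs come from the Sample size section: "A significance level of 5% and a sampling error (absolute) for the prevalence of 10% were assumed", and "expected prevalence between 50 and 70"%. With z = 1.96, p = 0.60 and e = 0.10, n = 3.8416 × 0.24 / 0.01 = 92.2. The stated number is reproduced (p = 0.50 gives 96.0 and p = 0.70 gives 80.7). Rounding up to 100 leaves room for (100 − 92.2)/100 = 7.8% loss. This calculation concerns acceptance and is unaffected by the present point.

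**2. Group sizes for illustration.** The Discussion states: "Our expectation is that almost 60% of the adolescents after childbearing at our hospital will choose the ENG-implant". Of 100 women that gives about 60 implant users and 40 others.

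**3. Three ways of counting losses, implant group only.** Assumption: about 84% of followed women continue, the implant adherence figure cited in the Background. The loss rate is not in the document, so a range is shown.

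| Lost of 60 | Losses excluded | Losses as discontinued | Losses as continuing |
|---|---|---|---|
| 3 (5%) | 48/57 = 84.2% | 48/60 = 80.0% | 51/60 = 85.0% |
| 6 (10%) | 45/54 = 83.3% | 45/60 = 75.0% | 51/60 = 85.0% |
| 12 (20%) | 40/48 = 83.3% | 40/60 = 66.7% | 52/60 = 86.7% |
| 18 (30%) | 35/42 = 83.3% | 35/60 = 58.3% | 53/60 = 88.3% |

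The spread between the last two columns equals the loss fraction.

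**4. Effect on the comparison.** Further assumption: about 60% of followed comparison women continue. Chi-square without continuity correction.

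| Loss, implant / other | Excluded | As discontinued | As continuing |
|---|---|---|---|
| 5% / 5% | 48/57 v 23/38, p = 0.009 | 48/60 v 23/40, p = 0.015 | 51/60 v 25/40, p = 0.010 |
| 20% / 20% | 40/48 v 19/32, p = 0.017 | 40/60 v 19/40, p = 0.056 | 52/60 v 27/40, p = 0.021 |
| 10% / 30% | 45/54 v 17/28, p = 0.024 | 45/60 v 17/40, p = 0.001 | 51/60 v 29/40, p = 0.126 |

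In the last row the difference is 22.6, 32.5 or 12.5 points. Fisher's test falls on the same side of 5% in every cell.

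**5. Complete cases against a life table.** Actuarial estimate: S = Π[1 − d/(n − c/2)], with d stopping and c lost in each interval.

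- Assumed: 60 implant users, removals 2, 4, 4 and losses 5, 4, 3 over the three visit intervals. S = (1 − 2/57.5)(1 − 4/51)(1 − 4/43.5) = 80.8%. Complete cases give 38/48 = 79.2%, a gap of 1.6 points. The two extreme counts are 38/60 = 63.3% and 50/60 = 83.3%.
- The 20% / 20% case of step 4, with losses split evenly before and after 6 months. Implant: (1 − 4/57)(1 − 4/47) = 85.1% against 83.3%. Others, with 7 then 6 stopping: (1 − 7/38)(1 − 6/27) = 63.5% against 59.4%, a gap of 4.1 points.

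**6. Expected pregnancies.** At the Background's failure rate of 0.4 per 100 women per year, 60 implant users followed for a year would have 60 × 0.004 = 0.24 pregnancies.

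**The case against.** **The spread is not the method's doing.** In step 5 the 20-point range comes from 12 losses among 60 women, and any estimator would face it. The life table moves the result by 1.6 points. This stands. A reader might infer that the stated tests put a 20-point error into the continuation rate, but neither the document nor the arithmetic supports that.

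**Loss may be small.** The allowance is 7.8%, women unable to attend are excluded, and telephone calls are planned. At 5% loss per group all three counts agree. This stands too, and so the effect is conditional on the loss rate.

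**Censoring is no cure.** If loss is related to stopping, Kaplan-Meier and log-rank results are biased as well. This is correct, and it is why bounds are needed alongside them.

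**The article is condensed.** A full plan may say how lost women are counted, so that silence is not held against the article. Nor does the article assign chi-square to continuation or pregnancy by name. It does, however, commit to tests for qualitative variables, these outcomes are qualitative, and chi-square/Fisher is the only test offered for them. Couple-year protection does not deal with censoring.

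**The loss rule may be meant sensibly.** The sentence can equally mean that both visit and calls must fail. A reader might infer that known continuation or pregnancy status will be discarded. The text does not say so; it only labels women as lost, and ambiguously.

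**Conclusion.** The point holds in a limited form. The tests stated for qualitative outcomes need a fixed denominator and waste the partial follow-up of women lost before 12 months, although continuation, discontinuation by reason and pregnancy over one year are compared outcomes and losses are foreseen. The wording of the loss rule is ambiguous and should be settled.

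The size cannot be fixed, because no loss rate is stated. Under the assumptions shown (60 and 40 women; about 84% and 60% continuing among those followed), it is small near 5% loss. At 20% loss in both groups, or 10% against 30%, the way losses are counted can carry the test across the 5% level. Using a life table in place of complete cases shifts the estimates by about 1.6 to 4.1 points in the examples. The larger swings measure uncertainty due to missing outcomes, which a better estimator makes visible but does not remove.

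**What to change.** - **Continuation:** estimate at 12 months by Kaplan-Meier or life table with a 95% confidence interval, from a stated time zero comparable in both groups, and compare by log-rank test.
- **Discontinuation by reason:** report cumulative incidence with the other reasons as competing events (Aalen-Johansen).
- **Pregnancy:** report a life-table or person-time rate with an exact confidence interval. Do not plan an adjusted Cox model, because events will be very few.
- **Censoring and loss:** censor at last contact, telephone included. Reword the Follow-up section so that a woman is lost only when both the visit and the three calls have failed.
- **Sensitivity:** because loss may be informative, give best- and worst-case bounds and report loss by group.

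The cost is slightly more analysis work and the use of dates of removal, stopping, conception and last contact. The data form is not shown, so it may already hold these dates. The SAS version named in the article has standard procedures for these analyses. Sample size and visit schedule need not change.
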